## **ii) Outcome measures**

### **Primary outcomes:**

1. Prevalence of anaemia
2. Education achievement assessed by a battery of tests of reading, writing and arithmetic

### **Secondary outcomes:**

3. Prevalence of malaria parasitemia
4. Concentration as assessed by classroom-based tests of sustained attention
5. Classroom behavior as assessed by teacher ratings of children's inattentive and hyperactive-impulsive behaviors.
6. School attendance as assessed by class attendance registers
7. Examination results as assessed by government examination scores

## **iii) Study sites**

The study will take place in rural primary schools in Kwale district, a hot and relatively dry area on the Kenyan coast. Continuous precipitation supports intense year-round transmission, with two seasonal peaks in malaria cases reflecting the bimodal rainfall pattern, with the heaviest rainfall typically occurring between April and June, with a smaller peak in October and November each year. Most malaria is caused by *Plasmodium falciparum*. A recent survey among 25 schools in 2008 found that the prevalence of malaria infection among schoolchildren in Kwale district was 9% (ranging from 1-28% by school), and 20% (3-37% by school) of children are anaemic ([name], unpublished data). Helminth infections are also common with 38% of schoolchildren estimated to be infected with hookworm and 41% infected with *Schistosoma haematobium*.

Kwale district also has some of the poorest educational indicators in the country, with the district having the worst KCPE examination scores for the last three years running.

## **iv) Study populations**

Children enrolled in participating schools will be assessed for the following eligibility criteria:

**1. Inclusion criteria**

- a. Pupil enrolled at participating schools in standards 1-5
- b. Provision of informed consent from parent or guardian
- c. Provision of assent by student

**2. Exclusion criteria**

- a. Pupils unwilling to participate in the study
- b. Known allergy or history of adverse reaction to study medications
- c. Known or suspected sickle-cell trait. These children will be referred to testing and/or clinical management as per national guidelines

**v) Sample size determination**

Power analysis was adjusted for clustering (Hayes & Bennett, 1999) and focused on two main outcomes of interest: the percentage of children who are anaemic (haemoglobin <110 g/L); and education achievement assessed by a battery of tests of reading, writing and arithmetic.

For anaemia, assuming a baseline prevalence of 20% (as found in the 2008 school surveys in Kwale), an intraclass correlation of between 0.025 and 50 children sampled per school, a sample size of 21 schools with a total of 1050 children of all ages in each arm was estimated to provide 80% power to detect a 25% reduction in anemia in the intervention group compared to placebo at 5% level of significance. This equates to 84 schools and 4200 children.

For educational achievement tests, an overall sample size of 100 schools with 50 children per school (5000 children overall) is sufficient to detect an effect size of 0.2 standard deviation (SD) assuming an intra-class correlation of 0.2 (ICC varied from 0.1 to 0.2 with mathematics and literacy tests in Class 2 in 210 schools in Western Kenya; ICC is expected to be lower in Class 1) and a correlation between baseline and final test scores of 0.7. This sample size is sufficient to detect an effect size of 0.15 SD for concentration tests, which have a lower intra-class correlation (0.07 in the previous study in Bondo).

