## **8. Design and Methodology**

### **i) General Study design**

This study will be a factorial-design, cluster-randomised, to assess the impact of IST and enhanced literacy instruction by teachers on the health and educational achievement of healthy schoolchildren. This study is one of two studies investigating the health and educational impact of malaria control, with a parallel study planned in Senegal, where malaria transmission is intense but highly seasonal.

The target population in this study includes children attending primary schools in Kenya. The accessible population includes the children attending the participating primary schools in standards 1-7 in Kwale district. The unit of analysis is the school. Schools will be randomized to one of four groups, receiving either the IST intervention alone, the education intervention alone, the IST and education interventions combined, or neither intervention. The first two arms would evaluate the impact of IST. The final two arms would investigate the hypothesis that IST helps children benefit from improved quality of education. Health and educational outcomes will be assessed before intervention and twelve and twenty four months later. The impact of each intervention will be estimated for education outcomes and health outcomes in separate multiple regression models. An interaction term will be included to identify any synergistic effects between the two interventions.

The survey data will be collected over two years – see section 10. Development and testing of survey instruments will take place in 2008. Baseline data collection and intervention activities will commence in January 2009, with follow-up surveys planned in 2010 and 2011. The study will be conducted by the Kenya Medical Research Institute in collaboration with the Division of Malaria Control in the Ministry of Public Health and Sanitation, University of Nairobi, the London School of Hygiene and Tropical Medicine, and Harvard University.

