#### **ix) Education and cost-effectiveness assessments**

Pre- and post-intervention education assessments will be performed in each school. This will involve a number of visits per year to each school. The first visit will occur one week prior to the biomedical assessments and will commence with classroom tests of attention for 30-60 minutes in standard 1 and individual assessments of pre-literacy and pre-numeracy skills. A team of 4 people can assess 60 children (2 classes) per day. With two survey teams, 10 schools can be surveyed per week and the pre-intervention surveys will be completed in all schools in 10-12 weeks. In the following term, the teams will return to conduct spot checks of attendance and to conduct classroom observations of pupil behavior and teaching methods. Two people can complete a school in one day and the assessment will take 5 weeks to complete. In the final term, the teams will return to conduct individual cognitive tests and detailed tests of literacy development. These tests will be on an individual basis and will take 4 testers 2 days to complete one school, taking around 15-20 weeks to complete.

Assessments will measure the foundational skills for literacy acquisition: specifically, letter knowledge, phonological awareness, print concepts, individual word reading, passage reading, and spelling. These foundational skills are recognized in the reading literature to be predictive of later reading acquisition in alphabetic languages. Furthermore, they are useful assessments because they are informative about a student's literacy knowledge and avoid floor effects. The assessments do not duplicate current MoE assessments. Instead, the current study will assess the literacy skills that are needed by a student if they are to meet the MoE goal that "the learners should acquire reading

skills to enable them to read and understand instructions, to read for information, and for pleasure (p. 55, Primary English Syllabus, 2002).

The method used to assess educational performance is appropriate for the local situation. People from the local community will be hired to serve as educational assessors. Since the assessments are administered individually, assessors will be trained to ensure children feel comfortable and can clarify the directions in the mother tongue. In addition, brief assessments are used in consideration of young children's attention spans.

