#### **Data analysis**

All analyses will be on the basis of intention-to-treat. To assess the success of randomization baseline characteristics between the four randomization groups will be compared. To assess the impact of the interventions, methods appropriate for cluster-randomized trials will be used (Hayes & Bennett, 1999). The prevalence, or mean, in each school will be calculated and the unadjusted risk ratio (RR), or mean difference (intervention-control), estimated in each stratum. An overall estimate of the effect of IST will be obtained by taking a weighted average of the stratum-specific estimates, the weights proportional to the number of schools per stratum, and 95% confidence intervals will be adjusted for observed between-school variance. Formal hypothesis testing will be undertaken using stratified unpaired t-tests. The impact of each intervention will be estimated for education outcomes and health outcomes in separate multiple regression models. An interaction term will be included to identify any synergistic effects between the two interventions. Statistical analysis will be carried out using STATA® software, version 10.0. (Stata Corporation, Texas, USA).

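### The 0.15 SD detectable effect for concentration tests needs baseline adjustment, but the formal test in the protocol is an unadjusted t-test on school means; the primary achievement figure has the same mismatch

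*Protocol*

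**What the plan says.** Protocol section 8.v sizes the education part at "an overall sample size of 100 schools with 50 children per school (5000 children overall". It claims 0.2 SD for the achievement tests with an ICC of 0.2 and "a correlation between baseline and final test scores of 0.7". The next sentence turns to attention: "This sample size is sufficient to detect an effect size of 0.15 SD for concentration tests". The reason it offers is a smaller ICC for these tests, 0.07, taken from the earlier Bondo study. It gives no correlation, power or sidedness for that outcome. Power and significance level appear only for anaemia, where the sample is said to "provide 80% power to detect a 25% reduction in anemia in the intervention group compared to placebo at 5% level of significance".

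Section 9 (Data analysis) summarises each school by its prevalence or mean, with "the unadjusted risk ratio (RR), or mean difference (intervention-control), estimated in each stratum", and gives formal hypothesis testing to unpaired t-tests that respect the strata. It then says that effects will also be estimated in multiple regression models. The only model term it names is the interaction between the two interventions.

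Section 8.ix schedules pre- and post-intervention education assessments. The first visit "will commence with classroom tests of attention for 30-60 minutes in standard 1". The same section has school performance tested before treatment.

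**The concern.** A power figure that relies on baseline correlation is earned only if the analysis uses the baseline. Section 8.v invokes such a correlation for achievement and leaves it unclear for concentration. The formal test in section 9 uses no baseline score for either.

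Sustained attention is the route by which the trial expects malaria control to reach learning: section 4(b) says that the earlier western Kenya trial improved attention but not achievement, and specific objective 3 tests attention. If the comparison is less sensitive than stated, a null attention result would be credited with power it did not have. The same holds for achievement, which is a primary outcome.

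**Working it through.** **Inputs.** From section 8.v: 100 schools, m = 50 children per school; ICC 0.07 (concentration) and 0.2 (achievement); r = 0.7 (stated for achievement). The factorial main effect of IST compares k = 50 schools with 50. Assumed for the education outcomes: two-sided 5% and 80% power, so the multiplier is 1.960 + 0.842 = 2.80. No dropout is allowed for.

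**Calibration on the anaemia figure.** 20% v 15% needs 906 children per side before clustering. Design effect: 1 + 49 × 0.025 = 2.225. Schools per side: 906 × 2.225 / 50 = 40.3, plus 1 for the Hayes–Bennett correction = 41.3, rounded up to 42. Two sides give 84, the protocol's total. The protocol's own arithmetic is therefore two-sided 5%, 80% power, on a main-effect comparison (2 × 21 schools per side).

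**Formula.** SE = sqrt(2 × [ICC + (1 − ICC)/m] × (1 − r²) / k). Detectable effect = 2.80 × SE. Power at effect d = Φ(d/SE − 1.96). Setting r = 0 gives the unadjusted test.

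**Concentration, unadjusted.** ICC + (1 − ICC)/m = 0.07 + 0.93/50 = 0.0886. SE = sqrt(2 × 0.0886/50) = 0.0595. Detectable effect: 0.167 SD (0.168 with t quantiles). Power at 0.15 SD: Φ(2.52 − 1.96) = 71%. Reaching 0.15 SD would take about 62 schools per side (63 with the Hayes–Bennett addition).

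**Concentration, r = 0.7.** SE = 0.0595 × sqrt(0.51) = 0.0425. Detectable effect: 0.119 SD. Power at 0.15 SD: 94%.

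**Correlation needed for 0.15 SD.** sqrt(1 − (0.15/0.1668)²) = 0.44. At r = 0.3 the detectable effect is 0.159 SD (75% power at 0.15 SD).

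**Achievement.** ICC + (1 − ICC)/m = 0.2 + 0.8/50 = 0.216. Unadjusted SE = sqrt(2 × 0.216/50) = 0.0930.

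| Outcome | Stated | Unadjusted (power at stated) | r = 0.7 (power at stated) |
|---|---|---|---|
| Concentration | 0.15 SD | 0.167 SD (71%) | 0.119 SD (94%) |
| Achievement | 0.2 SD | 0.260 SD (58%) | 0.186 SD (85%) |

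**Two sensitivities.** The factor (1 − r²) assumes that baseline explains variance equally between and within schools. With r = 0.7 acting only between schools, concentration detects 0.131 SD; acting only within schools, 0.158 SD. Separately, a one-sided 5% test would detect 0.148 SD unadjusted, but the anaemia calibration points to two-sided testing.

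**The case against.** The statement is one of sufficiency, so 0.15 SD need not be the exact minimum. It directly follows the sentence with the 0.7 correlation and names only the ICC as different. If 0.7 carries over, 0.119 SD is detectable and the statement is true with margin; that 0.119 differs from 0.15 is no contradiction. This stands. A reader might infer that the design detects 0.17 SD at best. The protocol does not support that, because 0.167 SD belongs to the unadjusted test only.

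Stratification could also help. Schools are stratified by examination performance (section 8.vi) and the t-test is stratified. If the strata removed about 24% of the between-school variance in concentration (residual ICC about 0.053), the unadjusted test would reach 0.15 SD: 2.80 × sqrt(2 × (0.0531 + 0.0186)/50) = 0.150. For achievement the share would have to be about 44% (residual ICC 0.111). The protocol gives no such share, so this is a possibility and not a rebuttal.

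Section 9 also mentions regression, section 8.ix plans covariates to raise power, and the covariate list may sit in a SAP that is not shown. But section 9 itself gives formal testing to the t-test and names no baseline term in the regression. The covariates listed in section 8.ix are mainly parental, teacher, school and socio-economic, not the child's own baseline score.

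Section 8.i says "The first two arms would evaluate the impact of IST", from which a reader might infer a 25 v 25 comparison: 0.236 SD unadjusted with 43% power at 0.15 SD, or 0.168 SD with 70% power at r = 0.7. The protocol does not support that as the design contrast. The 84 anaemia schools reproduce as 42 v 42, and 0.2 SD for achievement is met at 50 v 50 but not at 25 v 25. Read literally, the first two arms listed are IST alone and education alone, which is not IST against control. The wording needs reconciling, but it cannot carry a power figure.

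Finally, concentration is a secondary outcome and did not set the number of schools. That limits the consequence for attention. It does not limit it for achievement, which is primary and did set it.

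**Conclusion.** The point holds as a mismatch between the power paragraph and the formal test, not as an arithmetic error in 0.15 SD. Under the unadjusted test in section 9, the main-effect comparison detects about 0.167 SD, with 71% power at 0.15 SD. The claim becomes true if baseline scores enter the test with a correlation of about 0.44 or more, and section 8.v does not say which correlation was used for concentration. For achievement the shortfall is larger: 58% power at 0.2 SD without the baseline, against 85% with the correlation that the protocol itself assumes.

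This rests on two-sided 5% and 80% power for the education outcomes (stated only for anaemia, without sidedness), no gain from stratification, no dropout, and for the adjusted figures a correlation acting equally at both levels.

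**What to change.** 1. In section 9, make the formal test of attention and achievement scores baseline-adjusted: for example, a regression on the child's pre-intervention score that allows for clustering and strata, or a t-test on school-level residuals from such a regression.
2. In section 8.v, state the correlation, power, sidedness and main-effect contrast (50 v 50 schools) behind 0.15 SD, and the power behind 0.2 SD.
3. If the unadjusted t-test is kept as the formal test, restate the concentration figure as about 0.17 SD and the achievement figure as about 0.26 SD, unless a gain from stratification is stated and justified.
4. Reconcile the sentence in section 8.i about which arms evaluate IST with the factorial main-effect comparison.

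The cost is wording in three sections. The baseline attention and performance tests are already scheduled before the intervention in the cohort that starts in standard 1, so no new data collection or schools are needed. Adjustment is available only for children who took the baseline test.

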**vi) Randomization and treatment assignment and allocation**

Schools will be randomly assigned to one of the four intervention groups using a pre-defined stratified randomization procedure. A computer generated randomization list will be created by a member of the project who will not be directly involved in the conduct of the study. Sealed copies of the original randomization lists and documentation of the procedure used to generate the lists will be stored in KEMRI offices in Nairobi. Prior to the onset of the study, sealed copies of the randomization lists will be distributed to the member of the study team responsible for treatment allocation.

Schools will be stratified into five groups according to school examination performance in previous years, to account for differences in school quality and socio-economic environment. Five schools will be randomly selected from each school-performance stratum, and within each stratum schools were randomly allocated to 1 of 5 coded drug groups using block randomization according to the randomization listing.

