## 3. Abstract

The Government of Kenya is committed to improving the education of its children, and recognizes the importance of child health for educational achievement. While malaria represents one of the main health problems afflicting Kenyan schoolchildren, the evidence base for policy development and programme implementation for school-based malaria control remains inadequate. A recent study in western Kenya showed that delivering intermittent preventive treatment (IPT) to schoolchildren improved rates of anaemia and classroom concentration, but did not improve school performance. This study aims to (i) investigate the impact of a related malaria prevention strategy, intermittent screening and treatment, on health and education among schoolchildren in a different malaria transmission setting and (ii) determine the interaction between health and improved literacy instruction. The study will be undertaken in 100 randomly selected primary schools in Kwale District. IST will consist of all children being screened using rapid diagnostic tests (RDTs) for malaria once a term (thrice yearly). Children (with or without malaria symptoms) found to be RDT-positive will be treated with artemisinin-based combination therapy (ACT). Screening and treatment will be administered by district health workers. The education intervention will involve a programme of training for primary school teachers to improve literacy instruction. The study is designed to detect a 25% reduction in anaemia and an improvement of 0.2 standard deviations in mathematics and literacy tests. Additional outcomes will also be measured including malaria parasitaemia, classroom attention and school attendance. Health and educational outcomes will be assessed before intervention and twelve and twenty four months later. Information will also be collected on in-vivo parasitological efficacy of treatments and the cost-effectiveness of intervention. The findings of this study will provide critical information on the effectiveness of interventions to reduce the health and education burden of malaria among school-aged children.

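### The allocation rule in section 8 vi gives 25 schools in five groups, which contradicts the 100-school, four-arm factorial design

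*Protocol*

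**What the plan says.** Protocol section 8 vi opens with "Schools will be randomly assigned to one of the four intervention groups using a pre-defined stratified randomization procedure". Its second paragraph then sets the strata, "Schools will be stratified into five groups according to school examination performance in previous years", and the selection, "Five schools will be randomly selected from each school-performance stratum", and continues: "within each stratum schools were randomly allocated to 1 of 5 coded drug groups using block randomization".

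Other sections describe a different size and arm structure:

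- Section 3 (Abstract): "The study will be undertaken in 100 randomly selected primary schools in Kwale District".
- Section 8 i: "Schools will be randomized to one of four groups, receiving either the IST intervention alone, the education intervention alone", with the combined and the no-intervention groups making up the four.
- Section 8 v: "an overall sample size of 100 schools with 50 children per school (5000 children overall" for the education outcome; for anaemia, 21 schools per arm, and "This equates to 84 schools and 4200 children".
- Section 8 vii: the education programme goes to half of the IST schools and half of the controls. The two interventions are RDT screening with treatment of positives, and teacher training.
- Section 15: achievement is measured in 100 schools, and the literacy programme runs in 50.

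Section 9 (Data analysis) builds on the strata. Effects are estimated stratum by stratum, combined with weights proportional to the number of schools in each stratum, and tested with stratified unpaired t-tests.

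**The concern.** Section 8 vi is the only place in the protocol that says how schools are selected and allocated. Whoever prepares the randomisation list is, by the same section, not directly involved in running the study, and so depends on what this text says. It gives that person two incompatible group counts (four and five), a number of schools that fits no other section, and a unit of allocation, the coded drug group, that section 8 vii does not define.

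At stake are the arm structure behind the two main effects and the interaction, and the strata that the section 9 estimator and tests use. Allocation has to be settled before randomisation. If the text stays as it is, a later reader cannot check whether the list followed the protocol.

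**Working it through.** **Inputs.** From section 8 vi: 5 strata, 5 schools selected per stratum, 5 groups in the second paragraph and 4 in the opening sentence. From section 8 v: 100 schools for education, 84 for anaemia, 50 children per school, anaemia prevalence 20% with a 25% reduction (to 15%), ICC 0.025 (the only value printed), education effect 0.2 SD, ICC 0.2, baseline-final correlation 0.7. From section 15: 50 literacy schools. Assumed here: two-sided 5% and a normal approximation.

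**1. Is the sample size section at fault?** For 20% v 15% at 80% power, the usual two-proportion formula gives 906 children per side.

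- Design effect: 1 + 49 x 0.025 = 2.225.
- Schools per side: 906 x 2.225 / 50 = 40.3. Adding 1 for the Hayes-Bennett correction gives 41.3, so 42.
- Total: 2 x 42 = 84, or 21 per factorial cell.

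The plan's 84 reproduces as an IST main-effect comparison. The fault is therefore in section 8 vi.

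**2. Can section 8 vi be reconciled with the rest?**

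| Reading | Result | Fits? |
|---|---|---|
| 5 strata x 5 schools, 5 groups | 25 schools, 5 per group | No: a quarter of 100, below 84, and not a 2 x 2 |
| 5 strata x 5 schools, 4 groups | 25 / 4 = 6.25 per group | No: not whole schools, and 5 per stratum does not divide by 4 |
| 100 schools, 5 groups | 20 per group | No: not a 2 x 2, and below the 21 per arm of section 8 v |
| 5 schools per arm per stratum, 4 arms | 5 x 4 x 5 = 100 | The total fits, but it is not what is written, and five groups are still named |

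Under the first two readings the 50 literacy schools of section 15 would be twice the number of schools in the trial.

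**3. What the stated design implies with equal strata.** 100 / 5 = 20 schools per stratum; 20 / 4 = 5 per arm within each stratum; 5 x 5 = 25 per arm; 50 v 50 for each main effect.

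**4. Hypothetical power if only 25 schools were randomised.** This takes the 25-school count and imposes a two-sided split of about 12.5 v 12.5, a layout that no section states.

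Anaemia: SE = sqrt[(0.20 x 0.80 + 0.15 x 0.85) / n_eff], with n_eff = schools per side x 50 / 2.225.

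- 12.5 per side: n_eff = 281, SE = sqrt(0.2875 / 281) = 0.032, 0.05 / SE - 1.96 = -0.40, power about 35%.
- 50 per side: n_eff = 1124, SE = 0.016, 0.05 / SE - 1.96 = 1.17, power about 88%.

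Education: design effect 1 + 49 x 0.2 = 10.8; residual variance 1 - 0.7² = 0.51 (the correlation applied to total variance); SE = sqrt[2 x 10.8 x 0.51 / (schools per side x 50)].

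- 12.5 per side: SE = 0.133, 0.2 / SE - 1.96 = -0.45, power about 33%.
- 50 per side: SE = 0.066, 0.2 / SE - 1.96 = 1.05, power about 85%.

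**The case against.** The strongest defence is that this is a drafting slip with an obvious intended meaning. If five schools was meant per arm within each stratum, then 5 strata x 4 arms x 5 schools = 100, with 25 per arm and 50 literacy schools, exactly as elsewhere. With the 100-school total in three sections, four groups in two, and the 84 schools reproducible, nobody is likely to randomise 25 schools. This stands as a limit on the consequences. It does not clear the text: the words do not say per arm, and the five coded drug groups would still be wrong.

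A reader might infer from the past tense and the drug coding that the paragraph was carried over from another trial. The protocol does not say so. What can be shown is the contradiction.

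A reader might also take the 35% and 33% as the expected result of this plan. They are not. Followed literally, the text gives five groups of five schools, which is no two-level comparison at all. The figures belong to a hypothetical split.

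Nor is it enough to say that the trial plainly has no coded drug. Sections 6 and 8 v name a placebo comparator, section 15 budgets for placebos, and section 8 xiii provides for unblinding, yet section 8 vii defines no placebo. The inconsistency therefore reaches beyond this one paragraph.

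**Conclusion.** The point holds as an internal contradiction in the only stated allocation rule: 25 schools against 100 (and against the 84 needed for anaemia), five groups against four, and a coded drug that the interventions section does not define. That conclusion needs only counting and no statistical assumption. It is more than clerical, because the rule governs how the list is generated and which strata enter the section 9 analysis, so it must be corrected. The factorial design and the sample size are not in question.

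Any loss of power is conditional on 25 schools actually being randomised. It rests on a two-sided 5% level, a normal approximation, ICCs of 0.025 and 0.2, and the 0.7 correlation acting on total variance.

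**What to change.** Rewrite the second paragraph of section 8 vi so that the schools selected per stratum, the number of groups and the block structure give 100 schools in four arms. With equal strata, one consistent version is 5 strata, 20 schools selected per stratum, and 5 allocated to each arm within each stratum. Section 9 weights by schools per stratum, so unequal strata are not ruled out. If the sponsor intends them, the number in each stratum should be stated.

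Replace the five coded drug groups with the four intervention groups named in section 8 i. Reconcile the placebo wording in sections 6, 8 v and 15, and the unblinding provision in section 8 xiii, with the interventions as section 8 vii defines them.

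Make sure the randomisation list follows the corrected rule. The protocol does not establish whether a list already exists; if it does, check it against the new text. The cost is protocol wording plus that check, with no schools beyond the 100 planned.
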